***b) Rationale for inclusion of vulnerable populations:***

NA. While MS patients are considered ill they are not considered a vulnerable population.

***c) Sources of Materials:***

This is a double-blind placebo controlled study. The study investigators, research associates involved in subject assessment, and subjects will have no knowledge of study assignment. Data analysis will be performed blinded to treatment status. The General Clinical Research Center (GCRC) at OHSU houses a biostatistics resource center that will create the randomization scheme and will ensure blinding of all study medications and data records. Study medication will be handled, labeled, and distributed by pharmacists in the Investigational Drug Service who are not involved in either the outcome assessments or data analysis. We will also evaluate the effectiveness of our blinding by giving both study evaluators and subjects a short questionnaire asking about knowledge of group assignment. If a subject reports serious side effects related to the study medication and information on group assignment is believed to be necessary for the subject’s safety and well being, the blind will be broken for that subject. The randomization code will otherwise be broken only after data analysis or if there are numerous reports of serious adverse events before the end of the study. To insure confidentiality, all data sources will be coded with a unique identification number that has no personal identifying information. All study files will be stored in locked cabinets in the trial coordinator’s office. Computer data will be protected with passwords known only to the appropriate staff. All data obtained from this study will be used for research purposes only.

Data will be collected at eight points during the course of the study.

***d) Potential Risks:***

The risks to subjects participating in this study are minimal. The risks may include mild anxiety from filling out questionnaires, and mild side effects from fish oil or placebo capsules. Subjects may feel some pain when blood is drawn. There is a small chance the needle will cause bleeding, a bruise, or an infection. There have been few reports of adverse events in people taking up to 15 grams of fish oil per day [45]; we do not anticipate serious adverse events from fish oil supplementation using a dose of 6.0 grams per day. Because fish oil does have antiplatelet and antithromboxane A2  levels, there is a concern about increase bleeding time and interactions with blood thinning medications (e.g. warfarin). However, a study evaluating the effects of 1 year of fish oil supplementation on patients undergoing artery bypass reported no increase in bleeding during surgery in patients given fish oil plus aspirin or given fish oil plus warfarin compared to patients given those therapies alone [46]. In one double-blind, placebo-controlled trial of people with current or past history of ventricular tachycardia or ventricular fibrillation receiving implantable cardioverter defibrillator (ICD) or patients that had received an ICD or ICD therapy for an episode of VT/VF, it was reported that the group receiving fish oil at 1.8 grams/day had an increase risk of VT or VF compared to those receiving placebo [49]. Because of this potential risk, we are excluding patients with this condition and patients taking anti-arrhythmia medication from the study.

***e) Recruitment and Informed Consent:***

Recruitment will occur after the Institutional Review Board at OHSU approves the study.

Subjects with MS will be recruited from the greater Portland metropolitan area in the form of mailings to MS Center of Oregon patients, mailings to neurologists, advertisements on the MS Center of Oregon website and in the newsletter of the Oregon chapter of the National MS Society (NMSS). The Oregon Chapter of the NMSS has a statewide mailing list of over 5,000 members and has assisted the MS Center in recruitment for both CAM and conventional intervention studies. Consent will be obtained during the screening visit, which will occur at the MS Center of Oregon. [name] or a research assistant will go over the entire consent form with the potential subject and will be available to answer any questions. [name] or the research assistant will then ask the potential subject if they understand the purpose of the study and the risks and benefits associated with the study. The potential subject will have the opportunity to take the informed consent home to review. No testing or examinations will be performed before the consent form is understood and signed. A second informed consent will be obtained in the same fashion from subjects who qualify and are willing to participate in the continuation phase of the study.

*f) Protection against risk:*

The Data Safety and Monitoring Board of ORCCAMIND will monitor this study to ensure the safety of subjects. We will monitor adverse events by laboratory tests, which include prothrombin time (PT/INR) and comprehensive metabolic panel. For the first month of the study general health events, worsening of depression (>30 on BDI), and suicidal ideation (question # 9 on BDI) will be monitored weekly (2 x by phone and 1x in-clinic) for all subjects. If either of these occurs the subject will be immediately referred for standard care and will be exited from the study. [name] will be available by pager 24 hours a day to address patient safety issues. [name] will be available to discuss these cases with [name]. After the first month, subjects will be monitored every other week for general health events, worsening of depression (>30 on BDI), and suicidal ideation (question # 9 on BDI) (1 x by phone and 1x in-clinic). The same procedures described for month-1 will apply for all subjects throughout the study period. Subjects that have an acute MS exacerbation during the study will be referred to their neurologist for care.

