#### Visit 6 (week 8)

MADRS and BDI will be administered. A research assistant will assess the subject for adverse events and perform a pill count. The subject will also be asked about any changes in medication

or doses of medications (prescribed and over the counter). The subject will be instructed to bring their medication bottle to their next scheduled visit.

Visit 7 (week 12)

This visit will assess all of the same measures as Visit 2. In addition, the subject will return all remaining study drug and a pill count will be performed. If the subject has achieved a 50% improvement on their BDI or MADRS score they may choose to continue on in the study for another 3 months or to exit the study. If the subject chooses to remain in the study, we will review the consent form for Phase II of the study and attain consent before proceeding with Phase II. After being consented the subject for the subject will receive another month’s supply of study medication and will be instructed to bring this bottle to their next scheduled visit.

Table 1. Study Schedule: Phase I

| **Assessments** | **Visit 1**  Screen | **Visit 2**  Baseline | **Visit 3**  Wk 0 | Phone  Wk 1 | **Visit 4**  Wk 2 | Phone  Wk 3 | **Visit 5**  Wk 4 | **Visit 6**  Wk 8 | Phone  Wk 10 | **Visit 7**  Wk 12 |
| --- | --- | --- | --- | --- | --- | --- | --- | --- | --- | --- |
| Family and Medical Hx | X |  |  |  |  |  |  |  |  |  |
| PE/Neurological exam/EDSS |  | X |  |  |  |  |  |  |  | X |
| SCID | X |  |  |  |  |  |  |  |  |  |
| BDI | X | X |  | X | X | X | X | X | X | X |
| MADRS | X | X |  |  |  |  | X | X |  | X |
| MMSE | X |  |  |  |  |  |  |  |  |  |
| MSQLI |  | X |  |  |  |  | X |  |  | X |
| MSFC |  | X |  |  |  |  |  |  |  | X |
| Cytokine measurement |  | X |  |  |  |  | X |  |  | X |
| Metabolic panel, PT time |  | X |  |  |  |  | X |  |  | X |
| RBC fatty acid |  | X |  |  |  |  | X |  |  | X |
| Food freq. survey |  | X |  |  |  |  |  |  |  | X |
| Concomitant medications | X | X |  |  |  |  | X | X |  | X |
| Adverse Events |  |  | X | X | X | X | X | X | X | X |
| Pill Count |  |  |  |  |  |  | X | X |  | X |
| Blinding evaluation |  |  |  |  |  |  |  |  |  | X |

Table 2. Study Schedule: Phase II

| **Assessments** | Month 4 | | Month 5 | | Month 6 | |
| --- | --- | --- | --- | --- | --- | --- |
| Phone  wk  14 | Visit 8 wk  16 | phone  wk  18 | Visit 9 wk  20 | phone  wk  22 | Visit 10 wk  24 |
| Family and Medical History |  |  |  |  |  |  |

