#### Statistical Analysis Statistical power and sample size

The study that used 2g/day of E-EPA reported a 9.3-unit difference between baseline and 4-week differences in placebo and active groups for the HDRS, this difference was statistically significant (p < 0.001) [5]. The standard deviation for the groups was 7.4 (the larger of the standard deviations). A sample size of 11 subjects per group provides 80% power with an alpha= 0.05, to detect the above difference in HDRS between the treatment and placebo group. A sample size of 18 subjects per group will provide power greater than 95% with an alpha= 0.05, to detect a difference of 500 units for IFN- levels between baseline and post-treatment levels. This assumes a standard deviation of 400 units and is based on the results of a study that reported a decrease in IFN- levels in MS patients with MDD from baseline values after 16-wks of either therapy based or medication based treatments for depression [8]. Assuming a dropout rate of 20% the sample size of 60 subjects, or 30 per group is also more than adequate to detect a treatment difference in IFN- levels produced from PBMC. The additional sample will provide additional power for the exploratory analyses using the regression analysis. We are using the MADRS as the primary outcome measure as it is highly correlated with the HDRS [26-28] and will be more sensitive to treatment change in patients with MS than the HDRS. As we expect MADRS scores to have a greater change with treatment than the HDRS, we are well powered with 60 subjects.

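### Safety checks are promised every two weeks after month 1, but Table 1 schedules no contact between week 4 and week 8

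*Protocol*

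**What the plan says.** Section E.f (Protection against risk) sets the monitoring frequency in two steps. In the first month subjects "will be monitored weekly (2 x by phone and 1x in-clinic) for all subjects". From then on the interval is two weeks: "After the first month, subjects will be monitored every other week for general health events, worsening of depression (>30 on BDI), and suicidal ideation", with the mode of contact given as "1 x by phone and 1x in-clinic". A BDI score above 30, or suicidal ideation on BDI question 9, leads to immediate referral for standard care and exit from the study.

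Table 1 (Study Schedule: Phase I) is where these contacts are laid out. From week 4 onward its header reads "Visit 5 Wk 4 | Visit 6 Wk 8 | Phone Wk 10 | Visit 7 Wk 12". The BDI row reads "BDI | X | X | | X | X | X | X | X | X | X", with one cell for each of the ten time columns. The Adverse Events row has no entry between weeks 4 and 8 either.

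Table 2 (Study Schedule: Phase II) starts with a telephone contact at week 14 and continues "Visit 8 wk 16 | phone wk 18 | Visit 9 wk 20 | phone wk 22 | Visit 10 wk 24".

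**The concern.** The text and the schedule table give different instructions for the second month, and the protocol does not say which one governs. Site staff normally work from the schedule table. If they do so here, a subject who worsens or develops suicidal thoughts just after week 4 has no planned screen until week 8.

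The population makes this more than a matter of tidiness. Subjects have SCID-diagnosed major depressive disorder. The upper randomization stratum admits screening BDI scores up to 30, so a subject can enter one point short of a score that triggers exit. The exclusion for suicidality is worded around severe depression with both ideation and a plan, so lesser ideation is not clearly excluded at entry. Antidepressant treatment is meant to stay stable, and a change or increase ends participation. The scheduled screen is therefore one of the main ways to find a subject who needs ordinary care.

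**Working it through.** The check compares the contact weeks in the two tables with the interval in section E.f. No power or sample-size formula is involved.

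**Inputs**
- Required interval: weekly in month 1, two-weekly afterwards (section E.f).
- Scheduled on-treatment contacts: weeks 0, 1, 2, 3, 4, 8, 10 and 12 (Table 1), then 14, 16, 18, 20, 22 and 24 (Table 2).
- Enrolment of 60 and planned dropout of 20% (Statistical power and sample size: "Assuming a dropout rate of 20% the sample size of 60 subjects").

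**Intervals between successive contacts**

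| Period | Contact weeks | Intervals (weeks) | Required (weeks) | Agrees? |
|---|---|---|---|---|
| Month 1 | 0, 1, 2, 3, 4 | 1, 1, 1, 1 | 1 | Yes |
| Month 2 | 4, 8 | 4 | 2 | **No** |
| Month 3 | 8, 10, 12 | 2, 2 | 2 | Yes |
| Phase II | 12, 14, 16, 18, 20, 22, 24 | 2, 2, 2, 2, 2, 2 | 2 | Yes |

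**Size of the gap.** 4 × 7 = 28 days, against 2 × 7 = 14 days.

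**Checks missing.** In Phase I after week 4, checks are due at weeks 6, 8, 10 and 12. Those scheduled are at weeks 8, 10 and 12. Thus 1 of 4 is absent, and it is week 6. For subjects who go on to Phase II, checks are due at weeks 6, 8, …, 24, which is (24 − 6)/2 + 1 = 10, and 9 are scheduled. The same single contact is missing.

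**Subjects affected.** At most 60. If the whole planned dropout had occurred by week 4: 60 × (1 − 0.20) = 48. The protocol gives no timing for dropout, so 48 to 60 is a range under that assumption.

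**Could the column have been lost when the table was read from the PDF?** This is unlikely. The Table 1 header has ten time columns, and the BDI and Adverse Events rows each have ten matching cells. A lost week 6 column would have had to vanish from the header and all the rows together. The visit-by-visit narrative also passes from Visit 5 (week 4) to Visit 6 (week 8). That adds little, because the narrative describes clinic visits and does not list the telephone contacts that Table 1 does contain.

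**The case against.** The best counter-argument is that this is a slip in one table and that the intent is clear. Section E.f states the frequency plainly as a commitment for all subjects, the two-week rhythm appears everywhere else after month 1, and a missing column does not cancel the commitment. There are also other safeguards: BDI screens at weeks 1, 2, 3 and 4 for anyone reaching the gap, a 24-hour pager, a data safety and monitoring board, and entry limits that keep out the most severe cases. The documents offer no basis for estimating how many events one missing call would fail to catch.

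Much of this is fair. The omission does look unintended, and the 28-day interval arises only if the table is followed. But the table is the working instrument. The pager depends on the subject calling, and a monitoring board does not screen individuals. Neither replaces a planned BDI.

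Two side points should not be pressed. The sentence "The same procedures described for month-1 will apply for all subjects throughout the study period" most naturally refers to referral and exit. If it referred to frequency, it would contradict the two-weekly rule just before it, so it is not evidence for a week 6 contact. The counts by mode of contact are also loose. For month 1 the text gives two calls and one clinic check, whereas Table 1 has two calls (weeks 1 and 3) and two clinic visits (weeks 2 and 4). The firm conflict is the stated two-week interval against the gap from week 4 to week 8.

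**Conclusion.** The point holds. Table 1 does not implement the monitoring interval that section E.f promises, and the discrepancy is confined to one contact, at week 6. If the table is followed, each of 48 to 60 subjects goes 28 days between safety screens where 14 were promised. The lower figure assumes that all planned dropout falls before the gap. The upper figure assumes none.

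This is a subject-safety inconsistency and has no bearing on the efficacy outcomes or their analysis. It should be fixed because the missing contact is a suicidality and worsening screen with a defined action attached. It does not call the trial's design into question.

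**What to change.** Add a telephone contact at week 6 to Table 1, between Visit 5 and Visit 6, and mark the BDI and Adverse Events rows exactly as for the week 10 call. Leave the two-weekly commitment in section E.f as it stands. Contacts then fall at weeks 4, 6, 8, 10 and 12, all two weeks apart, and months 2 and 3 each have one call and one clinic visit, as Phase II already does. The planned count of seven Phase I visits is unchanged, because telephone contacts are not numbered as visits.

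The cost is one table column and one call per subject, 48 to 60 calls in all, of a kind already planned at weeks 1, 3 and 10.

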***g) Potential Benefits of the Proposed Research to the Subjects and Others:***

Identifying safe and effective therapies that can decrease depression for those that are not responding well to antidepressant medication is of potential benefit for people with MS. In addition, fish oils have anti-inflammatory properties that may also have potential benefits for MS, which is an inflammatory condition of the CNS. Fish oils have also been reported to decrease triglyceride levels, so this therapy may be very beneficial to subjects that are at risk for cardiovascular disease.

**h)** ***Importance of Knowledge to be Gained:***

Complementary and alternative medicine (CAM) use is high in people with MS, yet there is little scientific evidence on the safety and effectiveness of CAM in this population. This is a pilot study aimed at collecting preliminary data on the safety and effectiveness of fish oil as an adjunct therapy for depression in MS. Data collected from this study will aid in the construction of a larger double-blind placebo controlled trial designed so we can better evaluate the effects of fish oil supplementation in depression and better understand the mechanism by which fish oil may exert its clinical effects.

